### Quantitative Data Collection and Sample Size

The health facility checklist was developed in collaboration with study partners based on the updated Bangladesh guidelines for PSBI management, which focuses on capturing health systems data on service availability, general service readiness, and service-specific readiness [15, 21]. The evaluation team piloted the checklist in July 2015 and adapted questions prior to baseline data collection. The baseline checklist was administered prior to the government’s rollout of the guidelines in 31 selected health facilities in Sylhet and Lakshmipur. The baseline checklist assessed facility readiness to implement the new guidelines including the availability of staff, drugs, and equipment. UH&FWCs were excluded if the SACMO post was vacant at the time of the baseline health facility assessment. A total of 9 UH&FWCs were selected in Zakigonj and Kanaighat, Sylhet, and 10 UH&FWCs were selected in Ramgonj, Lakshmipur. The health facility checklist was administered at two additional time points during the study period, 4 months after the start of implementation and then at the end of the study (August 2016). Data collectors also visited the UH&FWC weekly to abstract data from facility records on the number of young infants that sought services. This activity provided utilization data including the number of young infants classified with signs of infection, frequency of follow-up, and treatment received.

Rolling household surveys were administered to explore infant illness and care-seeking history, maternal knowledge, and maternal perception of severity of danger signs. Household screening and the survey were conducted by a trained group of CHWs in the study areas from November 2015-August 2016. CHWs recruited for this study identified all recently delivered women and their live born babies (0–59 days) in the included catchment areas by visiting all households during the two monthly scheduled home visits. Only married women of reproductive age (MWRA) (13–49 years) having a live birth as a pregnancy outcome and residing in the selected unions during the study period were eligible to participate in the household survey. It took approximately 2–3 months to screen and administer the survey in all the 19 UH&FWC catchment areas. Thus, a MWRA with a young infant could only be enrolled in the survey once during the study period. The household survey questionnaire was developed utilizing questions from previous household surveys, which were administered in the Sylhet study area and published by the Projahnmo research group [18, 22, 23]. The population size in our study areas is ~ 250,000 in each of the districts with an annual birth cohort of 6250 (2.5% CBR). Based on our previous estimates, we expected that 38% of young infants will be sick as per mother’s reports for at least once in the first 2 months of their life [24]. Applying this estimate, there will be ~ 2375 cases of reported sickness in a 1-year period in each of the areas.

We estimated current rates of care-seeking for sick young infants from union health facilities to be 4% based on previous data. We required 76 sick infants in each round of the survey to estimate the increase of care-seeking from union facilities from 4% at baseline to 20% at end line with 80% power. Our primary outcome was reported sickness and care-seeking in the preceding 14 days on the day of survey. All women that delivered a live birth in the preceding 60 days of the date of survey were asked to participate in the morbidity and care-seeking surveys if caregivers were able to recall illness episodes. Applying 38% cumulative incidence of reported infant illness in the first 2 months of life, we expected 9% of caregivers to report infant illness in the 14-day recall period. Thus, we targeted 845 caregivers of young infants to identify 76 sick infants in each round of the survey. Assuming a response rate of 80%, which allows for an estimated 20% rate of refusal or caregiver absence at the time of the household visit, we targeted an estimated 1055 caregivers of young infants per round of the survey (every 2–3 months). In order to achieve this target sample size, we screened all women of reproductive age for inclusion in the survey throughout the study period.

The study team also aimed to follow-up all young infants managed under the updated guidelines to assess compliance with follow-up, treatment outcomes, and safety of the regimen. Facility utilization data were collected through weekly review of the sick infant registers at the UH&FWC by our study team to assess the number of infants classified with infection, referrals, and treatment data. The study team used these records to identify young infants for follow-up in the community. To measure treatment compliance assuming 50% compliance rate with 10% precision and accounting for 10% loss to follow-up, we required complete data from follow-up with 107 young infants treated for infection in each study area. Assuming 12% average care-seeking, we estimate that about 285 sick young infants will seek care from union level facilities (12% of 2375 expected cases). However, we aimed to follow-up all young infants diagnosed and managed under the new infection management guidelines to measure the safety of the program, which will also provide compliance data. Follow-up of sick young infants was continuous throughout the study period as the aim was to follow-up all young infant diagnosed with infection.

The total sample size requested for this study was estimated at 13,590 subjects. To obtain this sample size in the community, we obtained permission to screen 50,000 women of reproductive age in each study area totaling 100,000 women of reproductive age during the study period.

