Prior to national scale-up of the guidelines, the Bangladesh MoHFW planned to learn from implementation of the policy in three selected districts of Bangladesh: Kushtia, Lakshmipur, and Sylhet. We conducted an implementation research study in the first year of this program (September 2015–August 2016) to document the inputs and processes required for operationalization of the updated policy in varying contexts, identify barriers and facilitators for implementation, and integrate these early lessons into the plans for national scale-up. This paper describes the implementation research protocol followed by the Projahnmo and MaMoni Health System Strengthening (HSS) teams who provided support to the MoHFW in Sylhet and Lakshmipur, respectively. A third partner provided support in Kushtia, but their methodology is not described in this paper.

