## Discussion

This article describes the design of an implementation research study, which included support to the Bangladesh MoHFW to implement revised guidelines for the management of young infants suffering from PSBI and a mixed-methods evaluation. The evaluation aimed to identify facilitators and barriers to the implementation of the guidelines in first-level health facilities to inform scale-up. The WHO guidelines are intended to be adopted by national governments and implemented by health workers in limited resource settings. Thus, there is a need to study how these guidelines will be implemented outside of randomized controlled trials. Implementation research provides an opportunity to understand what, why, and how interventions work in real-world conditions [29]. Our incorporation of implementation research outcomes provides the opportunity for us to assess why the program was successful or unsuccessful in meeting goals, which will be valuable feedback for both the MoHFW, WHO, USAID, and other global stakeholders [30–32]. WHO is coordinating additional implementation research studies for PSBI guideline rollout in Pakistan, India, Nigeria, Malawi, DRC, and Ethiopia. Findings from this study will be disseminated among program managers, policy-makers, development partners, and other stakeholders.

The strength of this study is the use of both quantitative and qualitative approaches to provide a deeper understanding of the research questions than either method separately [33, 34]. This approach is well-suited to the implementation research because it provides a way to understand multiple perspectives and multiple outcomes grounded within local context [29, 35].

Given the lack of a control group and short study period, it will not be possible to causally link implementation support activities to observed changes in the population. For the household survey, this limitation is exacerbated because we do not have survey data collected prior to the MoHFW’s rollout of the PSBI guidelines in the study areas. It is important to note that the lack of a comparison group and lack of randomization make the study more vulnerable to internal and external threats to validity. We aimed to improve internal validity by collecting data at multiple points in time. However, our study period was limited to 1-year, which was necessary based on the GOB’s plans for scale-up.

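### The stated 80% power is for a 4% baseline survey round that the design does not contain; between survey rounds it holds only if round 1 is still near 4%

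*Protocol article*

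**What the plan says.** All references are to the protocol article.

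- **Sizing (Quantitative Data Collection and Sample Size).** "We required 76 sick infants in each round of the survey", in order to "estimate the increase of care-seeking from union facilities from 4% at baseline to 20% at end line with 80% power". The significance level and sidedness are not stated.
- **Source of the 4% (same section).** "We estimated current rates of care-seeking for sick young infants from union health facilities to be 4% based on previous data".
- **Recruitment that follows (same section).** "Thus, we targeted 845 caregivers of young infants to identify 76 sick infants in each round of the survey". Allowing for 80% response, this becomes 1055 caregivers per round, with a round every 2–3 months.
- **Outcome (same section).** The primary outcome is reported sickness and care-seeking over a 14-day recall.
- **Timing.** The Background gives the first programme year as September 2015 to August 2016. For the survey: "Household screening and the survey were conducted by a trained group of CHWs in the study areas from November 2015-August 2016".
- **Acknowledged gap (Discussion).** For the household survey, "we do not have survey data collected prior to the" rollout of the guidelines. This is given as something that worsens the difficulty of linking observed changes causally to the support activities.

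The one baseline collected before rollout is the health facility checklist. It records facility readiness, not care-seeking in households.

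**The concern.** A two-sample calculation with equal groups presupposes that both proportions are measured, each in its own sample. Here the second sample is the end-line round, and the first would have to be a survey round at the pre-rollout rate. The earliest available round starts about two months into the programme year, takes 2–3 months to complete, and asks about illness in the preceding 14 days. It therefore measures care-seeking after implementation has begun.

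If care-seeking has already risen by then, a first-versus-last comparison understates the total change and has less power than stated. This is the primary outcome, and the study is meant to inform national scale-up. A non-significant difference between rounds could be read as no increase, because the text promises adequate power for an increase from 4%.

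**Working it through.** **Inputs.** From the sample-size section: p1 = 0.04, p2 = 0.20, power 80%, 76 sick infants per round, equal rounds. Assumed because not stated: two-sided alpha of 0.05.

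**1. Reproduce 76.** With the pooled-variance formula and mean proportion 0.12:

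- n = [1.960 × √(2 × 0.12 × 0.88) + 0.842 × √(0.04 × 0.96 + 0.20 × 0.80)]² / 0.16²
- n = (0.9007 + 0.3749)² / 0.0256 = 63.6
- Continuity correction: n' = (n/4) × [1 + √(1 + 4/(n × 0.16))]² = 75.5, rounded up to 76.

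This matches the plan's figure exactly. The normal-approximation power at 76 per round is 80.3% with the correction and 86.6% without. The arithmetic is correct for the contrast it describes.

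**2. Check the follow-on figures.** 76 / 0.09 = 844.4, given as 845. 845 / 0.80 = 1056, given as 1055. So the recruitment target is derived from the same two-round contrast.

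**3. Compare the timeline with the contrast.** The programme year starts in September 2015 and the survey in November 2015. No round lies before rollout, and the Discussion says so. The 4% therefore cannot be the observed proportion of a baseline round in this survey.

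**4. Power between round 1 and end line at other first-round rates.** The documents give no expected first-round rate, so this is a range of assumptions. End line is kept at the plan's 20%. Power is by exact enumeration of both binomials at two-sided 0.05, given as Pearson / continuity-corrected.

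| Assumed round-1 rate | 76 per round | 152 per round (76 per area, pooled) |
|---|---|---|
| 4% | 90% / 85% | not needed |
| 6% | 76% / 68% | not needed |
| 8% | 58% / 49% | 87% / 83% |
| 10% | 42% / 33% | 69% / 63% |

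The exact values at 4% lie a few points above the normal-approximation values in step 1; the pattern is the same. By the plan's own continuity-corrected formula, 80% power against 20% would need 104 per round at a first-round rate of 6%, 147 at 8% and 219 at 10%.

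**5. One way to place round 1.** If the rise from 4% to 20% were linear over 12 months, the rate at month m would be 4% + 16% × m/12: 6.7% at month 2, 8.0% at month 3 and 8.7% at month 3.5. A linear path is compatible with the 12% average care-seeking used elsewhere in the section, since (4% + 20%)/2 = 12%, but the article does not state one.

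**The case against.** **The gap is disclosed.** The Discussion says plainly that no survey data precede rollout and that causal linkage is not possible. That stands, and it makes this a matter of an unreconciled figure rather than a hidden defect. But the disclosure concerns attribution. It does not say that the power statement no longer applies, and it does not say how the external 4% enters the comparison.

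**A reader might infer that real power is about half.** The documents do not support that as a fact. It needs a first-round rate of about 8–9% and also needs 76 to be the whole round. A slow start is plausible: community health workers were oriented during the first months of implementation, and drug supply was on an interim footing while government channels were arranged. At 6%, power is still 76% / 68%.

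**76 may be per area.** The text does not say. With 6250 births a year in each area, about 6250 × 60/365 = 1027 infants aged 0–59 days are present in each area at any time, close to the 1055 target. On that reading, and with the areas pooled, power stays at 83–87% for a first round at 8%. This bears on the size of the loss, but not on the absence of a baseline round.

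**End line can be set against the external 4%.** It can. If 4% is treated as a fixed value, a rule of 7 or more care-seekers among 76 has one-sided alpha 0.032 and power 99.7% at 20%. It would be too strong to say that no contrast with 4% is possible. But this is a different test from the one sized, and it ignores the uncertainty in the 4% and whether the earlier data are comparable.

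**Planning on a historical rate is ordinary practice.** Agreed. The difficulty lies in stating power for a contrast with a baseline round that will not be observed.

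**Conclusion.** The point holds in a limited form. The 76 is correctly calculated, but for a comparison that the survey rounds cannot supply. The 80% power statement holds between rounds only if round 1 is still near 4%. How far power falls is unknown, because the article gives no first-round rate and does not say whether 76 is per area. For first-round rates of 4% to 10%, it runs from 90% / 85% down to 42% / 33% at 76 per round; pooling two areas of 76 restores it to 87% / 83% at 8% and 69% / 63% at 10%. These figures assume two-sided alpha of 0.05, 20% at end line and independent observations.

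The figure needs correcting as written because it supports the primary outcome. The documents do not establish that the study is underpowered by any particular amount.

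**What to change.** In the section Quantitative Data Collection and Sample Size:

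1. Remove the claim of 80% power for a baseline-to-end-line contrast between survey rounds.
2. Label the 4% as an external planning value with its own uncertainty, not as a baseline measured in this survey.
3. State whether 76 (and hence 845 and 1055) is per study area or overall.
4. Restate power over a range of plausible first-round rates, as in the table above.
5. Describe the survey comparison as change after rollout, preferably using all rounds, for example a trend over months since rollout. Cross-refer to the limitation in the Discussion.

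Facility registers from before September 2015 should not be offered as a substitute baseline. They hold visits, without the community denominator of sick infants that the survey proportion needs.

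The cost is rewording and a less favourable stated power figure. No new data collection is required.

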### Qualitative data collection and sampling

Qualitative data collection took place concurrently during the study period to assess program feasibility and acceptance of the guidelines among MoHFW providers, managers responsible for program implementation, and caregivers of young infants. Among providers, perceptions of PSBI treatment at first-level facilities were collected using semi-structured IDIs with SACMOs and FPIs. We also conducted FGDs with FWVs. The SACMO at each of the selected UH&FWCs was asked to participate in at least one, but no more than two IDIs during the study period. Interviewers asked SACMOs and FWVs about their experience with the guidelines, opinions on training and routine supervision, and facility functioning. IDIs with FPIs were conducted in the last round of data collection (June–August 2016) to explore challenges with follow-up of infants in the community.

A subset of caregivers was selected from the list of all caregivers with young infants identified in the study area for FGDs as part of the qualitative component of this study. We aimed to explore community perceptions of young infant illness, care-seeking behaviors for illness episodes, and perceptions of care at the UH&FWC. For FGDs, caregivers were selected through convenience sampling of mothers (13–49 years) of infants under 6 months of age who were willing and able to share their experiences with care-seeking for infant illness. The number of participants for each focus group ranged from six to eight mothers.

Caregivers of sick young infants receiving outpatient treatment for PSBI were followed up in the community to assess treatment compliance. We aimed to conduct in-depth interviews with a subset of 30 of these caregivers in each study area throughout the study period. We purposively selected caregivers for interviews based on their infant’s categorization of infection. We conducted IDIs with caregivers of infants for each category of infection (i.e., critical illness, clinical severe infection, fast breathing as a single sign, and local bacterial infection). The goal of these interviews was to assess the caregiver’s experience with outpatient treatment, and reasons for non-compliance to the prescribed treatment and follow-up visits.

### Stakeholder workshops

This implementation research study adopted an adapted action learning cycle approach, or a “plan-do-study-act” (PDSA) cycle, also known as the Deming Cycle [25, 26]. According to the PDSA approach, program implementation was studied periodically, which provided implementers with an opportunity to identify and address implementation challenges in real-time. With each cycle, data were collected on the program implementation strengths and challenges and were reviewed by a group of stakeholders. The stakeholders then developed solutions to address the challenges identified in the previous cycle and implemented these changes in the subsequent cycle (Fig. 2). The successes and challenges of the revised program approach were studied in the subsequent cycle. We arranged a stakeholders’ meeting following each round of data collection, during which the preliminary results were reviewed, and stakeholders assessed the implementation progress and challenges. The records from the stakeholder meetings served as documentation of the program learning and were reported alongside the results from data collection activities. The evaluation team worked closely with the implementation support team and the MoHFW implementers to perform all the preparatory works and organized stakeholder review meetings for sharing and gathering inputs.

**Fig. 2 Fig2:**
[figure not shown]
Adapted “plan-do-study-act” cycle including study activities at each stage. This implementation research study adopted an adapted action learning cycle approach, or a “plan-do-study-act” (PDSA) cycle [25, 26] to guide program learning and inform adjustments to implementation support

A total of two stakeholder workshops were held in Dhaka after the first and third round of data collection, in January and September 2016, respectively. These workshops aimed to bring together implementation and study partners, district level officials, and stakeholders at the central level to share findings related to both successes and challenges that arose during the process of implementing the new guidelines. Through these workshops, participants shared early learnings from implementation support and evaluation activities and worked together to develop solutions to better support the implementation of the new guidelines.

### Data Analysis

Quantitative data were entered and stored in Microsoft SQL server and analyzed using Stata Special Edition 14 (College station, Texas, USA) [27]. The analysis plan for this data included summary statistics of distribution and cross-tabulation of indicators using the appropriate tests for significance (e.g., Student’s *t* test and chi-square). Qualitative data were analyzed following an adapted Framework approach [28] for identification of inductive and deductive themes. A codebook was developed to ensure consistency in the broader thematic concepts that was sought in the data. Johns Hopkins University (JHU) qualitative researchers applied thematic codes systematically to the data and examined for patterns. The interviews were transcribed and translated into English. The JHU qualitative team coded the English transcripts and analyzed as per a framework for analysis based on the objectives of the program and its implementation.

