### Implementation research methods

Over the course of the 1-year implementation research study (September 2015–August 2016), we conducted an evaluation, independent of the implementation support, which employed mixed-methods data collection activities in 19 unions located in two sub-districts of Sylhet (9 unions) and one sub-district of Lakshmipur (10 unions). A convergent parallel mixed-methods design was used to guide quantitative and qualitative data collection, analysis, and interpretation of study results. Quantitative data were collected through rolling household surveys, periodic health facility assessments, weekly extraction of data from health facility records of young infants, and continuous follow-up surveys with caregivers of infection cases in the community. Qualitative data were collected through process documentation activities, in-depth interviews with senior level program implementers, in-depth interviews (IDI), and focus group discussions (FGD) with UH&FWC service providers, and IDI and FGD with caregivers. Both quantitative and qualitative data activities were used to assess each study objective (Table 2).

**Table 2 Tab2:** Data collection activities by study objective

Study objective	Data collection activities	
	Quantitative	Qualitative
Examine feasibility of implementation of the newly developed infection management guidelines in young infants at UH&FWCs through outpatient services when referral is not accepted	• Health facility assessment	• IDI & FGD with UH&FWC service providers • IDI with MoHFW program implementers • Process documentation of implementation support activities
Assess the acceptability of infection management services delivered on an outpatient basis at UH&FWCs among the parents and families of young infants	• Follow-up surveys with caregivers of infection cases in the community	• IDI with caregivers of infection cases
Measure caregiver’s knowledge and coverage of infection management for young infants	• Household survey with caregivers of young infants	• FGD with caregivers of young infants
Assess the compliance of the families to the referral advice and new treatment regimen for young infant infections delivered at UH&FWCs	• Weekly review of young infant records at UH&FWC • Follow-up surveys with caregivers of infection cases in the community	• IDI with caregivers of infection cases

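### Neither sample size carries a design effect and the only tests named assume independent observations, although the data are clustered in 19 unions and the facility checklist is repeated

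*Protocol article*

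**What the plan says.** The section Implementation research methods states that the study "employed mixed-methods data collection activities in 19 unions located in two sub-districts of Sylhet (9 unions) and one sub-district of Lakshmipur (10 unions". The Background describes one union health and family welfare centre (UH&FWC) in most unions, staffed by one SACMO and at least one FWV. One UH&FWC per study union was selected, 9 in Sylhet and 10 in Lakshmipur.

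The section Quantitative Data Collection and Sample Size sets two targets:

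- **Household survey.** "We required 76 sick infants in each round of the survey" to detect a rise in care-seeking at union facilities "from 4% at baseline to 20% at end line with 80% power". This becomes 845 caregivers per round (9% reporting illness), and then "we targeted an estimated 1055 caregivers of young infants per round of the survey" after allowing for 80% response.
- **Compliance.** "To measure treatment compliance assuming 50% compliance rate with 10% precision and accounting for 10% loss to follow-up", the requirement is 107 infants per study area. The team nevertheless aimed to follow up every managed infant and expected about 285 per area.

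The only inflations mentioned are for non-response and loss to follow-up. The same section says of the facilities, after a baseline round: "The health facility checklist was administered at two additional time points during the study period".

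The Data Analysis section promises "summary statistics of distribution and cross-tabulation of indicators using the appropriate tests for significance" and offers Student's t test and chi-square as examples. It mentions no clustered or paired method.

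**The concern.** Whether a family uses the union facility, and whether it completes treatment started there, depends partly on that facility and its SACMO, who classifies, refers, treats and follows up. Outcomes within a union are therefore likely to be correlated. With positive correlation, 100 infants from 9 or 10 facilities carry less information than 100 independent infants. The stated precision and power are then optimistic, and unadjusted intervals are too narrow.

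The checklist raises a separate issue. Repeated measurements on the same facilities are paired, and in their ordinary form the two named tests are for independent samples.

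This matters because the Background says the early lessons are to feed into plans for national scale-up. Uncertainty about compliance and care-seeking should not be understated there.

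**Working it through.** **1. Reproducing 107.** Inputs from the article: p = 0.50, half-width 0.10, loss 10%.
1.96² × 0.25 / 0.10² = 96.04, and 96.04 / 0.9 = 106.7, so 107. This is simple random sampling.

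**2. Reproducing 76.** Inputs: 4% and 20%, 80% power. Two-sided 5% is assumed because the article gives no alpha. The two-proportion formula gives 64 per round (63.6 before rounding up). With the continuity correction it gives 75.5, so 76. Then 76 / 0.09 = 844.4 (845) and 845 / 0.8 = 1056 (stated as 1055). No design effect enters at any step.

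**3. Compliance with clustering.** Design effect DE = 1 + (m − 1) × ICC, where m is the number of infants per facility. Half-width = 1.96 × √(0.25 × DE / n). The ICC is assumed to lie between 0.02 and 0.10.

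| Completed follow-ups per area | Facilities | m | DE at ICC 0.02 / 0.05 / 0.10 | Half-width (points) |
|---|---|---|---|---|
| 96 (107 less 10%) | 9 | 10.7 | 1.19 / 1.48 / 1.97 | 10.9 / 12.2 / 14.0 |
| 96 | 10 | 9.6 | 1.17 / 1.43 / 1.86 | 10.8 / 12.0 / 13.6 |
| 256.5 (285 less 10%) | 9 | 28.5 | 1.55 / 2.38 / 3.75 | 7.6 / 9.4 / 11.9 |
| 256.5 | 10 | 25.7 | 1.49 / 2.23 / 3.47 | 7.5 / 9.1 / 11.4 |

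With DE = 1 the half-widths are 10.0 at 96 and 6.1 at 256.5. Following everyone improves the true precision, but it widens the gap between the true interval and an unadjusted one.

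**4. Care-seeking power.** The same unions are surveyed each round, so part of the union effect cancels in the change. Assuming half of it is shared across rounds, DE = 1 + (m − 1) × ICC − m × ICC × 0.5. Power is by exact enumeration at n = 76 / DE. With DE = 1 it is 85% with the continuity correction and 90% without.

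| Reading of 76 | m | ICC | DE | Effective n | Power, corrected | Power, uncorrected |
|---|---|---|---|---|---|---|
| Total over 19 unions | 4 | 0.05 | 1.05 | 72 | 82% | 88% |
| Total over 19 unions | 4 | 0.10 | 1.10 | 69 | 80% | 87% |
| Per district (about 9.5 unions) | 8 | 0.05 | 1.15 | 66 | 77% | 85% |
| Per district | 8 | 0.10 | 1.30 | 58 | 69% | 80% |

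The two-sided error of an unadjusted test is about 2 × [1 − Φ(1.96 / √DE)]. This gives 5.6% to 6.2% on the first reading and 6.8% to 8.6% on the second.

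**5. Two illustrations only.**
- *Comparing districts.* If maternal knowledge were compared between districts with 845 / 19 ≈ 44 women per union and ICC 0.05, DE = 1 + 43 × 0.05 = 3.15 and the unadjusted error would be about 27%. Nothing cancels here, because unions are nested in districts.
- *Checklist.* Suppose readiness rises from 8/19 to 14/19 facilities, with six gains and no losses. Fisher's exact test, treating the rounds as independent, gives p = 0.10. Exact McNemar gives p = 0.03.

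**The case against.** A reader might infer that the study's p-values are wrong. The article does not establish that. The two tests are introduced as examples under a promise of appropriate tests, in one sentence of a condensed article. A full analysis plan could specify cluster-adjusted and paired methods, and Student's t has a paired form. What stands is narrower: if the named examples are followed in their ordinary form, the error bars will be too small.

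A reader might also infer that the survey is clearly underpowered. It is not. Plain chi-square, the test actually named, keeps about 80% power or more throughout the assumed range. On the reading that 76 is a total, the corrected test also stays at about 80%.

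The 107 is a minimum, not the expected number. With about 285 cases per area, precision stays within ±10 points at ICC 0.05 and exceeds it only towards 0.10. No between-district test is specified, so the 27% figure describes an analysis the article does not commit to. The checklist example shows the unpaired test missing a change, not over-calling one.

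Finally, the 19 unions could be treated as fixed strata, with every household visited and every case followed. The Discussion says that generalizability was not a primary goal. That is coherent for describing these unions alone. It does not suffice once the results are used to plan national scale-up, because variation between unions is then part of the uncertainty.

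**Conclusion.** The point holds as a gap in the stated design, not as proof of wrong results. Both sample sizes assume independent observations; this follows from the article's own figures and does not depend on any ICC. The size of the effect does depend on one, and the documents give none.

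The firmest consequence is for compliance. At an ICC of 0.02 to 0.10, the ±10 points at 107 become about ±11 to ±14. At the expected 285 less loss they are about ±7.5 to ±12, against roughly ±6 from an unadjusted analysis.

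The effect on power for the change from 4% to 20% is modest. With half the union effect shared across rounds and ICC 0.05 to 0.10, corrected power is 82% to 80% if 76 is the total and 77% to 69% if it is per district. The article does not say clearly which is meant. Smaller ICCs would make all these losses smaller.

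**What to change.** - Analyse household and follow-up outcomes with union/UH&FWC as the cluster: mixed or GEE logistic regression with a small-sample correction for 19 clusters, or a Rao-Scott chi-square with union as the primary sampling unit. Include district as a fixed effect.
- Analyse the facility checklist with paired methods: exact McNemar, paired t, or a facility random effect across the three rounds.
- Restate the power for 76 and the precision for 107 with an explicit assumed ICC and design effect, and say whether 76 is per district or overall. Give the precision at the expected 285 as well.

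No new data are needed, since facility records and surveys are already organised by union. The cost is some analysis wording and slightly less favourable stated power and precision.
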